## Methods

### Study Design

The proposed study is a pilot, prospective, randomized, double-blinded, sham-controlled study to develop a frontal pole iTBS intervention. We will examine the safety, feasibility, tolerability, and efficacy of 10 sessions of iTBS over 2 weeks. Preliminary impulsivity, SI, and social and occupational functioning data will be collected before and after receiving active or sham treatment. In developing this protocol, we referenced the SPIRIT (Standard Protocol Items: Recommendations for Interventional Trials) guidelines [85]. We used the CONSORT (Consolidated Standards of Reporting Trials) checklist when writing our report [86]. Refer to Multimedia Appendix 1 for the CONSORT flow diagram.

### Ethical Considerations

The study protocol was reviewed and approved by the Edward Hines, Jr. VA Hospital Institutional Review Board (Hines IRB number 1716074) and the University of Illinois, Chicago Institutional Review Board. The study is registered on ClinicalTrials.gov (NCT05647044). This study is designed in accordance with the ethical standards of the US VA Office of Research and Development, based on those from the Declaration of Helsinki, the Belmont Report, US Common Rule and Regulations from the Council for International Organizations of Medical Sciences. The study will be overseen by the institutional review boards of the both Edward Hines, Jr. VA Hospital and the University of Illinois, Chicago. This research study is designed on a 5-year research plan.

A Health Insurance Portability and Accountability Act (HIPAA) authorization waiver will be obtained to enable electronic medical records review of potential participants before obtaining consent. The HIPAA waiver allows research staff to access information about the patient’s medical history and demographics, as well as history of drug or alcohol abuse to determine study eligibility. If a potential participant declines to participate in the study, no further contact will be made.

If the potential participant consents to the study, they will then begin the informed consent process. Informed consent will be obtained in English by trained research staff. Research participants will have access to research staff and the principal investigator to assist with any questions or concerns until understanding is achieved. A consent note is made in the participant’s medical record either electronically or on paper. The original consent is then placed in the medical record, a copy is given to the participant, a copy is filed with the Edward Hines, Jr. VA Hospital Institutional Review Board and the original informed consent is placed in the participant’s research binder and maintained in a locked file cabinet at Hines VA Hospital. Once the informed consent process is completed, a note will be documented in the electronic medical record system and the participant will be flagged as a research participant.

Any identifiable information about the participant, including their signed consent form, is stored in a different location than study data, on encrypted VA servers in files that are only accessible to approved study team members. The collected, deidentified research data are also stored on encrypted VA servers elsewhere, in password-protected folders, only accessible to approved study team personnel. Any participant information obtained in the study will be treated as confidential and safeguarded in accordance with the Privacy Act of 1974. Information published or presented about the results of the study will be done such that no individual identifying information is shared.

Participants will be compensated up to US $350 for their participation, prorated for their time.

### Participants

We will enroll 56 veterans aged between 22 and 65 years with a history of mTBI and impulsivity. They must also report that they have experienced SI within the last 3 months. mTBI will be defined according to the VA and Department of Defense guidelines [87] and use aspects of the mTBI symptom attribution and classification algorithm [88] when determining eligibility. mTBI must have occurred at least 1 year before enrollment to ensure that the injury has stabilized. Though it is not mandatory, veterans may also have diagnoses of depression, PTSD, or bipolar spectrum illness (without a history of psychosis). Recent SI (within the past 3 months) will be defined as a score of ≥1 on the Columbia Suicide Severity Rating Scale [89]. Impulsivity will be defined as having any mentions of impulsive behavior in the medical chart and any positive results on the Urgency, Premeditation (lack of), Perseveration (lack of), Sensation Seeking, Positive Urgency Impulsive Behavior Scale–Negative Urgency subscale (UPPS-P) [41]. For safety, we will exclude persons with contraindications to TMS or MRI because of increased risk of AEs. We will also exclude participants whose SI is active, with intent and plan, as they require emergency psychiatric intervention. We will not exclude individuals based on sex, gender identity, ethnicity, or race. To enhance generalizability, we will include veterans regardless of previous combat or deployment experience. As cannabis and alcohol use is prevalent among veterans, intermittent or low amounts of cannabis or alcohol consumption will not be considered exclusionary if the use does not meet the criteria for a moderate substance use disorder. Detailed information on inclusion and exclusion criteria is listed below (Textbox 2).

Participant inclusion and exclusion criteria.
**Inclusion criteria**
Aged between 22 and 65 yearsCan read and speak EnglishMild traumatic brain injury (mTBI) criteria: Symptom Attribution and Classification Algorithm [88] criteria for mTBI (without the requirement of clinical neuropsychological impairment).Columbia Suicide Severity Rating Scale score of ≥1 within 3 monthsHistory of impulsivity documented in the chart and exhibited on the Urgency, Premeditation (lack of), Perseveration (lack of), Sensation Seeking, Positive Urgency Impulsive Behavior Scale—Negative Urgency subscale (Urgency score >20) [41]
**Exclusion criteria**
Contraindications to intermittent theta burst stimulation or transcranial magnetic stimulation (eg, epilepsy)Contraindications to magnetic resonance imaging (eg, claustrophobia, ferromagnetic metal implants)Active substance use disorder per DSM-5 (Diagnostic and Statistical Manual of Mental Disorders, Fifth Edition) criteriaActive suicidal ideation with intent and plan (these participants will be brought to the emergency department for emergent psychiatric care)History of moderate to severe traumatic brain injuryHistory of nontraumatic neurological injury (eg, stroke, neurosurgery, hemorrhage)History of or current psychosis not due to an external cause (eg, due to illicit drug use)Pregnant or breastfeedingWithin 12 weeks of a major surgeryActive, unstable health condition (ie, decompensated heart failure, recent severe heart attack)Within 1 year of mTBI

### Power Analysis and Sample Size Justification

To ensure we have adequate power to detect a difference in our primary outcome, the Social and Occupational Functioning Assessment Scale (SOFAS), we conducted a power analysis. Assuming a significance level of 0.05, a mean SOFAS score of 44.6, and a SD of 15, with 50 veterans, we will have 82% power to detect a significant interaction between time and treatment assuming no change over time in the sham-iTBS group and a change of 13 points in the active iTBS group [90]. On the basis of similar studies of iTBS protocols for patients with depression and PTSD, receiving treatment of similar duration, attrition rates are expected to be low—under 10% [58,90,91]. As such, we plan to enroll participants to ensure we have an adequate sample size considering 10% attrition. Thus, our total sample size will be 56 with 28 in the active iTBS group and 28 in the sham iTBS group.

### Recruitment

We will recruit veterans receiving care from the TBI and polytrauma program, primary clinic, women’s health clinic, and the Mental Health Service Line at Edward Hines, Jr. VA Hospital in Hines, Illinois, United States. Personnel at all mentioned clinics will be educated on the study and encouraged to give institutional review board (IRB)–approved flyers containing contact information to veterans who may be a good fit for the study. We will be added as cosigners in the electronic medical records of Hines VA patients who may be deemed a good fit for this study. We will also mail informational letters to veterans who have completed past TBI studies and permit us to contact them about future studies through a TBI Data Repository (Hines IRB number14-003), which currently includes >300 veterans. Research candidates at the Hines VA will also be identified using administrative electronic health record data available through the VA Informatics and Computing Infrastructure. The VA Informatics and Computing Infrastructure database will search for TBI within the past 10 years (FY2013-FY2023) according to appropriate *International Classification of Diseases* (ninth and tenth editions), clinical modification, codes reflecting study inclusion criteria. All potentially eligible veterans will receive an informational letter and phone call to gauge interest and perform initial eligibility screens.

### Data Collection and Measures

#### MRI Data Acquisition, Neuronavigation, and Motor Thresholding

All participants will undergo an MRI of their brain before and after iTBS administration. Before iTBS, a high-resolution, 3D, T1-weighted, multigradient-echo sagittal anatomical scan (voxel size=0.8 mm isotropic resolution) will be collected at the University of Illinois, Chicago Center for Magnetic Resonance Research to allow for iTBS treatment site neuronavigation for each participant. Participants will also complete a resting-state functional MRI (fMRI) and diffusion tensor imaging before and after iTBS administration to examine treatment-induced connectivity changes. Participants will be asked to complete a standardized MRI safety screening form before starting the study to ensure the MRI safety procedures are followed (Multimedia Appendix 2).

Each participant’s T1 MRI will be loaded into a TMS Neural Navigator TS system (version 3.3.22, Localite), consisting of a camera and computer system that allows a TMS provider to superimpose an individual’s MRI onto where they are in space, allowing for very precise placement of the TMS coil. Electrodes will be placed on the thumb over the abductor pollicis brevis (ABP) muscle and connected to an electromyograph (MagVenture) to measure motor-evoked potentials (MEPs). To determine each participant’s motor threshold (MT) for iTBS (to determine at which intensity the iTBS stimulation should be delivered), a MagProX100 with MagOption stimulator and Magpro Cool Coil B65 A/P (MagVenture) will be used. Single pulse TMS will be administered to the left motor cortex at the hand knob. The location of this part of the motor cortex will be estimated using the participant’s MRI and then confirmed using TMS to identify the ABP muscle neural coordinates. The resting MT is the lowest stimulus intensity necessary to produce MEPs of the peak-to-peak amplitude of ≥50 µV in 5 of 10 trials. MEPs of the ABP will be recorded using surface electrodes on the right thumb. The right frontal pole will be identified and mapped using the TMS Neural Navigator (Localite) system. The anatomical location is easily identifiable using anatomical landmarks and correlates with electrode frontal polar cortex (FP; FP2) on a 10 to 20 electroencephalogram, a region overlapping with the right VMPFC [22,63,82]. Refer to Multimedia Appendix 3 for the equipment list.

#### Data Collection

Data collection is expected to take approximately 18 to 20 hours per participant over the intervention period of 2 weeks. Assessments will be collected at 4 time points in the study: screening, baseline, midpoint, and end point (Table 1).

**Table 1 table1:** Assessment timeline and purpose.

Assessment name		Assessment purpose	Items	Scoring	Validity and reliability
**Phone screening assessments**					
	Ohio State TBI^a^ Identification Method [92] (rater administered)	mTBI^b^ eligibility determination	Structured interview	Determination of the likelihood TBI sustained based on the participant’s detail recollection	Interrater reliability >90% (very high) [92]
	Columbia Suicide Severity Rating Scale [89] (rater administered)	History of suicidality, eligibility determination—secondary outcome	Five items measuring the presence of SI^c^, intensity of SI, presence of suicidal behaviors, lethality of behaviors	Ideation: 0-5; intensity: 2-25; suicidal behaviors: yes or no; lethality: 0-2, higher scores=more severe	Internal validity a=0.95 and test-retest reliability r_*tt*_*=*0.90-1.0 (very high) [93,94]
	Urgency, Premeditation (lack of), Perseveration (lack of), Sensation Seeking, Positive Urgency Impulsive Behavior Scale—Negative Urgency subscale [41,95] (rater administered)	Negative urgency impulsivity, eligibility determination—secondary outcome	Fifty-nine items measuring 4 traits–urgency, lack of premeditation, lack of perseveration, and sensation seeking [96]	4-point Likert scale questions, scored by each trait, some reverse-coded. Higher score=more severe [97]	Cronbach α=0.91 (very high) [41,97]
	Demographics (rater administered)	Sample characterization	—^d^	—	—
	UIC^e^ CMRR^f^ MRI^g^ Safety Form (Multimedia Appendix 2; rater administered)	MRI safety, compatibility, and eligibility determination	—	—	—
	TMS^h^ Safety Form (Multimedia Appendix 4; rater administered)	TMS safety compatibility, eligibility determination	—	—	—
**In-person screening assessments**					
	Structured diagnostic interview [88] (rater administered)	mTBI symptoms, eligibility determination	Structured interview	Likelihood symptoms owing to TBI sustained	—
	Neurobehavioral Symptom Inventory [98] (rater administered)	mTBI symptoms, eligibility determination	Twenty-two items asking about the severity of postconcussive symptoms	Severity: 0=never to 4=very severe, symptom always present; higher score=more severe symptoms	Cronbach α=0.81-0.96 (very high) [98]
	Clinically Administered PTSD^i^ Scale for DSM-5^j^ [99] (rater administered)	PTSD diagnosis	30-item questionnaire corresponding to DSM-5 PTSD criteria	Severity: 0=absent to 4=extreme, total symptom severity 0-80, higher score=more severe symptoms	Interrater reliability *K*=0.78-1.0 (high) discriminant validity: rs=0.02−0.54 (moderate) [100]
	Alcohol Use Disorder Identification Test [101] (participant self-administered)	Active alcohol use disorder, eligibility determination	10-item questionnaire about the frequency and amount of alcohol used	Questions 1-8 (0-4 points), 9-10 (0,2,4 points, range of 0-40 points, higher score=more severe symptoms)	AUROC^k^=0.891 (high) [101]
	Drug Use Disorders Identification Test [102] (participant self-administered)	Active substance abuse disorder, eligibility determination	11-item questionnaire about the frequency and number of drugs of abuse used	Questions 1-9 (0-4 points), 10-11 (0,2,4 points, total score 0-44, higher score=more severe symptoms)	Cronbach α=0.93 (very high), convergent validity *r*=0.76 (high) [102,103]
	Structured Clinical Interview for DSM-5, Research Version [104] (rater administered)	Active mental illness diagnosis	Structured interview	—	*K*>0.4 (above average) sensitivity of identifying diagnosis >0.8 (good) [105]
**Baseline, midpoint, and follow-up assessments**					
	Social and Occupational Functioning Assessment Scale [106] (rater administered)	Functioning in the community–primary outcome	Single item 100-point scale assessing social activities, relationships, self-care, aggressive behavior	0-100 (0=not functioning, 100=superior functioning)	Weighted *K*=0.95 (very high) [107]
	Columbia Suicide Severity Rating Scale (rater administered)	As described in “phone screening assessments”	As described in “phone screening assessments”	As described in “phone screening assessments”	As described in “phone screening assessments”
	Urgency, Premeditation (lack of), Perseveration (lack of), Sensation Seeking, Positive Urgency Impulsive Behavior Scale—Negative Urgency subscale (participant self-administered)	As described in “phone screening assessments”	As described in “phone screening assessments”	As described in “phone screening assessments”	As described in “phone screening assessments”
	Buss-Perry Aggressiveness Scale [108] (participant self-administered)	Aggression symptoms	29-item scale of true or false statements about aggressive and stable behaviors, including measures of physical aggression, verbal aggression, anger, and hostility	Scale of 1-5, 1 being “extremely uncharacteristic,” to 5 being “extremely characteristic.” Some reverse coded (stability statements), higher score=more aggressiveness	Test-retest reliability r_*tt*_=0.80 (high), Cronbach α=0.68-0.8 for each subscale (moderate-high) [108]
	Patient Health Questionnaire-9 [109] (participant self-administered)	Depression symptoms	9-item scale of DSM-5 depressive disorder symptoms (ie, low mood, sleep disturbance, SI)	Scale of 0-3, 0=“not at all,” 3=“always.” Higher score=more severe depression	Cronbach α=0.9 (very high) [110]
	Veteran’s RAND [111] (participant self-administered)	Perceived community functioning	36 items across 8 subscales of health including physical health, limitations owing to health, energy, social health, etc	0-100, higher score=more favorable health state	Cronbach α=0.78-0.93 depending on the domain (high-very high) [112]
	Beck Suicide Scale [113] (participant self-administered)	Suicidal ideation measurement	21 items about recent thoughts of death, recent suicidal behaviors	Scale of 0-2, higher number=more severe SI	Cronbach α=0.89 (very high), strong predictive validity [114]
	PTSD Checklist for DSM-5 [115] (participant self-administered)	PTSD symptoms	20 items corresponding to DSM-5 criteria for PTSD symptoms (eg, hypervigilance, flashbacks)	Scale of 0-4, 0=not at all, 4=extremely, score >33=probable PTSD diagnosis	Cronbach α=0.94 (very high) and test-retest reliability (r_*tt*_*=*0.82) (high) [116]
	Inventory of Depressive Symptomatology, Self-Report [117] (participant self-administered)	Depression symptoms	30 items assessing DSM-5 depressive symptoms	Scale of 0-3, 0=not present, 3=severe symptoms, higher score=more severe symptoms	Cronbach α=0.94 (very high) and test-retest reliability r_*tt*_*=*0.82 (high) [118]
	Difficulties in Emotion Regulation Scale [119] (participant self-administered)	Perceived struggles with emotion modulation	36-item scale, 6 subscales of emotion regulation	Scale of 1-5, 1=almost never, 5=almost always. Higher score=more difficulty with regulation	Cronbach α=0.90 (very high) [120]
	Delayed Discounting Task [121] (administered on computer)	Impulsivity inhibition measure	Behavioral assessment of impulsivity, 27 items where participant chooses smaller immediate rewards vs larger delayed reward	Tendency to choose smaller immediate rewards consistent with more impulsivity	Test-retest reliability r_*tt*_*=*0.89 (very high) [122]
	Stroop Color & Word Test [123] (rater administered)	Impulsivity inhibition measure	Behavioral assessment of processing speed and inhibition of cognitive interference	Measure the number of correct answers versus incorrect answers	Reliability estimates range from a=0.83 to a=0.91 and test-retest reliability ranges from r_*tt*_*=*0.79 to r_*tt*_*=*0.97 (all high-very high) [124]

^a^TBI: traumatic brain injury.

^b^mTBI: mild traumatic brain injury.

^c^SI: suicidal ideation.

^d^Not applicable.

^e^UIC: University of Illinois, Chicago.

^f^CMRR: Center for Magnetic Resonance Research.

^g^MRI: magnetic resonance imaging.

^h^TMS: transcranial magnetic stimulation.

^i^PTSD: posttraumatic stress disorder.

jDSM-5: Diagnostic and Statistical Manual of Mental Disorders, Fifth Edition.

^k^AUROC: area under the receiver operating characteristic curve.

Eligibility measures and information collected during the preenrollment phone screen administered by authorized clinical researchers include The Ohio State University TBI Identification Method [92], the Columbia Suicide Severity Rating Scale [89], the UPPS-P [41], self-reported age, the ability to read and speak English, the Center for Magnetic Resonance Research safety form (Multimedia Appendix 2), and TMS safety form (Multimedia Appendix 4). If deemed eligible, participants will be asked to complete an in-person screening.

The in-person screening will consist of completing additional assessments to ensure eligibility and baseline characteristics. They include the structured diagnostic interview from the symptom attribution and classification algorithm, created by individuals involved in this study to determine likelihood and severity of prior TBIs [88], the Neurobehavioral Symptom Inventory, to determine TBI-related symptom presence [98], the Clinician-Administered PTSD Scale for DSM-5 to determine preexisting diagnosis of PTSD [99], the Alcohol Use Disorder Identification Test-Consumption Questions to determine if an alcohol use disorder is present [101], the Drug Use Disorders Identification Test to determine if a drug use disorder is present [102], and the Structured Clinical Interview for DSM-5–Research Version to determine the presence of other psychiatric disorders [104].

Once the listed diagnostic and screening measures are completed and participants meet eligibility criteria, participants will be asked to complete self-reported measures at their baseline, midpoint, and end point visits (Table 1).

Feasibility completion rates will be described according to the reasons participants did not complete the 2-week intervention and the rates of missed sessions. Study completion is defined as completing all 10 sessions. Safety measures will follow procedures used in prior TMS studies [125] and will be scored using the *Medical Dictionary for Regulatory Activities*. Side effects, AEs, and the TMS data safety sheet will assess change severity throughout the intervention. Tolerability will be measured through the number of patients who complete the treatment course and via self-report.

#### Safety and AE Monitoring

Participants will participate in safety monitoring using the Data Safety Monitoring Scale. This scale will measure rate changes from baseline vitals (temperature, blood pressure, heart rate, oxygen saturation levels), fatigue, tinnitus (ringing in the ears), sleep, dizziness, nausea, vomiting, confusion, seizure, syncope (fainting), headache, neck pain, skin integrity of the scalp, and substance use.

Participants will be asked about AEs at each iTBS session, which will be logged to ensure safety throughout the intervention. These will be coded using the current version of the Medical Dictionary for Regulatory Activities, following procedures used in previous TMS studies [82]. The TMS safety sheet (Multimedia Appendix 4) will be collected and scored regarding severity and change from baseline. Data on every side effect and AE will be collected, rated on a score of 0 to 5 to assess severity, and reported.

All iTBS sessions will be videotaped to monitor for safety and allow for review in case of an AE. Acknowledgment for pictures and videos will be completed as part of our informed consent procedure.

AEs can be nonserious and serious. A serious AE is when the changes are life-threatening and may be disabling, require hospitalization, or require intervention to prevent impairment. We will measure deleterious changes in (1) neurological status and cognitive symptoms, (2) somatic and vestibular symptoms, (3) and depression. AE will be tracked using the AE log.

All unanticipated AEs related to this research study will be reported to the IRB, the study sponsor, and the research director within 5 business days. Serious AEs will be reported to these entities within 24 hours. If any unanticipated problem occurs, such as deviation from this protocol that involves risks or has the potential to recur, the investigator will report this information to the IRB. All AE information will be reported within 2 to 5 business days of the investigator or staff becoming aware of the event.

The study will take place at the Edward Hines, Jr. VA Hospital in Hines, Illinois, a full-service, tertiary-care hospital. Our laboratory is located within the rapid response area, meaning a team of specialized nurses and doctors can be called at any time to emergently assess a patient, should the need arise. Participants will be clinically monitored for seizure by trained research staff. In the event of a seizure, the research team member will call the on-site rapid response team (RRT) to provide emergent medical care to the participant. Cardiopulmonary resuscitation–trained research staff will assess the participant’s airway, breathing, and circulation until the RRT team arrives. RRT will then take over the participant’s care, including administering seizure-abating medications and airway protection, and transport the participant to the emergency department. Any seizure will result in stopping the intervention and withdrawal from the study.

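### In a trial that requires recent suicidal ideation, the printed serious-AE definition does not name death, the listed harms do not name suicidality or link the C-SSRS to the safety comparison, and the serious-AE reporting times need reconciling

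*Protocol article*

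**What the plan says.** All of the following is in the protocol article.

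- **Population** (Participants): "They must also report that they have experienced SI within the last 3 months".
- **Serious AE** (Safety and AE Monitoring): "A serious AE is when the changes are life-threatening and may be disabling, require hospitalization, or require intervention to prevent impairment".
- **Harms to be followed** (same section): "We will measure deleterious changes in (1) neurological status and cognitive symptoms, (2) somatic and vestibular symptoms, (3) and depression". The Data Safety Monitoring Scale covers vital signs and a list of symptoms that ends with "confusion, seizure, syncope (fainting), headache, neck pain, skin integrity of the scalp, and substance use". The rating before and after each session (Study Procedures) covers vital signs, sleep, fatigue, seizures and tinnitus.
- **Reporting times** (Safety and AE Monitoring): "All unanticipated AEs related to this research study will be reported to the IRB, the study sponsor, and the research director within 5 business days"; then "Serious AEs will be reported to these entities within 24 hours"; and at the end of the same paragraph, "All AE information will be reported within 2 to 5 business days of the investigator or staff becoming aware of the event".
- **AE capture** (same section): participants are asked about AEs at each session. Events are logged and coded in MedDRA, and each one is graded from 0 to 5 and reported, whether or not it is serious.
- **Suicidality measures** (Table 1): the C-SSRS is labelled as history of suicidality, eligibility and secondary outcome. The Beck scale is labelled as measuring suicidal ideation. Both are listed at baseline, midpoint and follow-up, as is the PHQ-9, a depression measure whose description includes suicidal ideation.
- **Safety analysis** (Analytic Plan): safety measures are described for all participants and compared between arms, with chi-square tests for categorical variables and t tests for continuous ones.

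**The concern.** The first central hypothesis is that frontal pole iTBS is safe in this population, and the abstract's conclusion promises preliminary evidence of safety. In people enrolled because of recent suicidal ideation, emerging or worsening suicidality is an obvious harm to compare between arms. The article prints its own serious-AE definition, its own list of harms and its own reporting deadlines, so these can be judged as written. Read together, they leave a death to be inferred. They also treat suicidality as something the treatment may improve, and never as something it may worsen. If so, the safety table could be complete by the plan's own rules and still not show, by arm, how many participants had worse ideation or any suicidal behaviour.

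**Working it through.** No figure in the plan needs reproducing. The check sets the passages side by side.

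**1. The definition, event by event.**

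- Death: not named. It can be reached only by reading it into the life-threatening clause.
- Life-threatening attempt: qualifies.
- Attempt leading to admission: qualifies.
- Behaviour that needs intervention to prevent impairment: qualifies.
- Suicidal behaviour that is not life-threatening and needs neither admission nor such intervention: not serious as defined, and not a named harm.
- New or worsened ideation without admission or intervention: not serious as defined, and not a named harm.

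**2. The harm lists.** The scale has 4 vital signs plus 13 further items (fatigue, tinnitus, sleep, dizziness, nausea, vomiting, confusion, seizure, syncope, headache, neck pain, scalp skin integrity, substance use), so 17. Items naming suicidal ideation, suicidal behaviour or death: 0 of 17. Domains of deleterious change naming them: 0 of 3. The nearest is depression. The section does not say which instrument measures that domain. The article's own rationale (TMS as Treatment for Suicidality) reports that change in suicidal ideation may be statistically independent of depression outcomes, so depression is a weak stand-in on the plan's own reasoning.

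**3. The link.** Table 1 gives the C-SSRS an eligibility and outcome role. Safety and AE Monitoring does not mention it. The Analytic Plan's safety sentences refer to safety measures, and no sentence makes the C-SSRS one of them. So the instrument that would detect the last two events in step 1 feeds neither the AE log nor the arm comparison as written.

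**4. Reporting times.** The serious-AE deadline is 24 hours. The sentence on all AE information gives 2 × 24 = 48 hours at the short end. The long end is 5 × 24 = 120 hours, or 7 × 24 = 168 hours when a weekend falls in between. Its shortest deadline is twice the serious-AE deadline, and serious events are not excepted. A report made inside 24 hours meets both, but the text sets two different latest times for one event. An event that is serious, unanticipated and related also falls under the 5-business-day sentence.

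**5. Scale, as illustration only.** The introduction (SI Epidemiology and Current Treatment) says that 5% to 10% of adults with suicidal ideation go on to an attempt. Assume that this is a one-year risk *a*, that it applies here, and that follow-up lasts *w* weeks. The per-person risk is p = 1 − (1 − a)^(w/52), and the chance of at least one attempt among 56 is 1 − (1 − p)^56.

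- a = 0.05, w = 2: p = 0.00197, expected 56p = 0.11, chance 10%.
- a = 0.10, w = 4: p = 0.00807, expected 56p = 0.45, chance 37%.

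Attempts are thus expected to be few. This says nothing about how often ideation worsens, for which the article gives no rate.

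**The case against.** The strongest reply is that nothing need go uncounted. AEs are asked about at every session, and each is logged, graded and reported regardless of seriousness. The arm comparison is not confined to serious events. The C-SSRS, the Beck scale and the PHQ-9 all touch on suicidality at midpoint and follow-up, and Study Procedures says that suicidality is tracked through the study. A condensed article may also leave AE-log procedures to the full protocol.

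Much of this stands, and it rules out several stronger readings that a reader might infer:

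- *That suicidal events would be missed.* Events raised at a session are recorded, and the scales observe suicidality.
- *That one attempt would be averaged into a group mean.* Table 1 scores C-SSRS behaviours as yes or no, and the Analytic Plan illustrates its mixed-model ANOVA only with the SOFAS. No sentence says that behaviours are averaged.
- *That a life-threatening event must also be disabling.* The clause is permissive. It is badly worded but does not plainly add a requirement.
- *That a 3-month recall applies after entry.* That window is an eligibility rule. The article gives no recall period for later assessments.
- *That the timing conflict hides events.* It concerns how fast they are notified. The last sentence names no recipient, so a specific-over-general reading is possible, though it is not stated.
- *That small-sample limits measure the defect.* With 28 on active, 0 events gives a one-sided 95% upper limit of 1 − 0.05^(1/28) = 10.1%, and one event is 1/28 = 3.6%. Both hold for any event under any definition.

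The reply does not dispose of the printed text. The article states a definition that omits death, states which harms will be measured, and states the deadlines. These are defects of what is written, not details left to a longer document.

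**Conclusion.** The point holds as one of classification and linkage. Death is not named in the serious-AE definition, and two criteria are merged. Suicidal ideation and behaviour appear in none of the 17 scale items and none of the three domains, and no sentence ties C-SSRS findings to the AE log or the between-arm safety comparison. The events most exposed are a death, which is left to inference, and worsened ideation or non-hospitalised behaviour detected on the scale but not raised as an AE. The separate conflict between 24 hours and 2 to 5 business days is real on the face of the text but concerns notification only.

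The documents do not support the conclusion that suicidal events will be lost from the safety result. No endpoint, sample size or model changes. What improves is the answer to the central safety hypothesis in the population for which it matters most. The verdict assumes that the article's printed wording reflects the protocol in force.

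**What to change.** 1. Name death in the serious-AE definition and list each criterion separately, joined by 'or'.
2. Add new or worsened suicidal ideation and any suicidal behaviour to the monitored harms.
3. In the safety results, tabulate the number of participants with each, by arm and with denominators, from the C-SSRS already planned at baseline, midpoint and end point. State the recall period for the post-baseline assessments. Make clear in Data Collection and Study Procedures that the rater-administered C-SSRS is included at those visits, since the text there mentions self-report measures and, at midpoint, neurocognitive testing.
4. Reconcile the 24-hour sentence with the sentence on all AE information and the 5-business-day sentence, so that each event has one stated deadline and recipient. Which deadline applies is for the sponsor and the review boards to settle.

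The cost is wording in the protocol and AE log plus one extra safety table, with no new instrument or visit. The article reports 2 participants enrolled as of July 2024, so a change made near that time would cover almost the whole sample. The table itself can be built from planned data at any point before analysis.
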